#### Pre-intervention experimental assessments

Eligible participants who qualify for the study undergo pre-intervention experimental testing (*Visits 3–5*; Figure 2) over a 2-week period; the numerical order of visits may be rearranged to facilitate scheduling. Subjects are asked to avoid major lifestyle changes including significant changes in physical activity (monitored via accelerometer; GENEActiv; 3-days recording) and time spent doing standard weekly activities (CHAMPS questionnaire), body weight, and diet (Automated Self-Administered 24-h diet recall; ASA24; National Cancer Institute) throughout the duration of the study. Subjects also are asked to record their diet for 24 h prior to their first pre-intervention outcome measure assessment visit. Subjects are asked to adhere as closely to this diet as possible prior to each future outcome measure assessment visit, both pre- and post-intervention, to control for acute diet-related changes to outcome measures. Subjects are asked to inform the research staff if there is a change in any lifestyle habits (either physician recommended or personal choice). Subjects are asked to maintain a stable medication regimen for the duration of the study, or to notify the research team should their physician recommend a change in medication during the study. Subjects are encouraged to notify their physician about their participation in the study.

Subjects are asked to follow the same pre-visit restrictions in *Visits 3–5* (pre-intervention testing) as followed for *Visits 1 &* 2 (screening assessments). Subjects also receive their initial allotment (2 weeks) of MitoQ or placebo pills during *Visit 5*. Assessments performed on the subjects during pre-intervention testing are summarized in Figure 2.

#### Randomization and blinding

Randomization is performed after subjects complete all screening measures, qualify for the study, and finish baseline testing. Although, we did not observe an obvious effect of subject (biological) sex or age on the change in FMD_BA_ with active treatment in our pilot study (Rossman et al., 2018): 1) the sample was likely too small (*n* = 20) to determine such effects; and 2) NIH requires that sex and other biological factors that may influence responsiveness be included in the analysis plan for purposes of rigor and reproducibility. Accordingly, block randomization has been employed based on biological sex (men and women) and age (60–70 years and >70 years). The study biostatistician developed the randomization tables and an unblinded research assistant, not involved with data collection or analysis, is responsible for individual subject group assignment. The CTRC nurses are blinded to the randomizations to maintain the integrity of the data and ensure accidental human error does not interfere with the randomization blinding. Investigative team members involved in the acquisition and analysis of outcome measurements are also blinded to group assignment.

#### Intervention administration and subject monitoring

Pill bottles containing either placebo or MitoQ are prepared and coded to keep subjects and investigators blinded to treatment condition. A member of the research team administers pills and provides dosing and timing instructions to subjects under the supervision of a CTRC nurse. Subjects are instructed to bring their pill bottles to each check-in visit (*Visits 6–8*; Figure 2) and post-intervention experimental visits (*Visits 9–11*; Figure 2) at which time a member of the research team counts the number of pills remaining in the container to assess adherence to the intervention.

During the intervention period, all subjects report to the CTRC once a month to meet with a CTRC nurse. The nurse asks subjects if they are experiencing any changes in their welfare and general health. The nurse also asks subjects if they are experiencing any side effects. The main side effect associated with MitoQ is gastrointestinal discomfort. As such, potential acute and chronic effects of MitoQ supplementation are assessed at all visits prior to and throughout the intervention using a symptom questionnaire and Visual Analog Scale (VAS). Subjects are instructed to contact the research coordinator or another member of the study team immediately if they develop any serious side effects or experience any change in their health. If subjects experience any serious unexpected side effects, they will be instructed to discontinue their respective intervention immediately. Transient minor side effects are closely monitored and continued participation in the study is determined by our physician of record.

#### Mid-intervention experimental assessment & protocol adherence

Following the completion of pre-intervention testing, the subjects return to the CTRC 2 weeks later for *Visit* 6 (Figure 2) to assess adherence to the protocol by returning previously received pill bottles (as discussed above); measure weight, resting blood pressure, and heart rate; complete a VAS; and receive a new allotment of pills for the next month.

One month later, subjects return to the CTRC for *Visit 7* for midpoint vascular testing. This testing includes measures assessing primary and secondary outcomes, including FMD_BA_, cfPWV, carotid compliance, intima media thickness, and β-stiffness index (Figure 2). *Visit 7* is 6 weeks from the start of the intervention and aligns with timing of measurements in our pilot trial with MitoQ supplementation (Rossman et al., 2018). To assess whether a longer duration of MitoQ supplementation (3 months) leads to a greater improvement in vascular function, midpoint vascular testing is performed and the change in endothelial function after 6 weeks will be compared with the change after 3 months of supplementation.

Subjects are asked to follow the same pre-intervention, pre-visit restrictions for *Visit 7*. In addition to midpoint vascular testing, subjects return pill bottles to assess adherence and receive an additional 1-month allotment of pills; bodyweight, blood pressure and resting heart rate are assessed; and subjects complete a symptom questionnaire and VAS.

One month later, subjects return to the CTRC for their final check-in visit, *Visit 8* (Figure 2). This visit is identical to *Visit 6*, except subjects receive enough pills to complete the remainder of the treatment.

#### Post-intervention experimental assessments

After completing 3 months of either MitoQ or placebo supplementation, participants return to the CU Boulder CTRC for post-intervention experimental assessments (*Visits 9–11*; Figure 2). Throughout post-intervention testing, subjects continue their respective intervention until the completion of post-testing. Subjects are allowed to take MitoQ or placebo the day before visits when outcomes are assessed (i.e., >10 h before testing) but asked to refrain from taking MitoQ the morning of testing to avoid acute effects on experimental testing. Subjects are asked to take their daily dose after their visit on testing days. *Visits 9–11* are identical to *Visits 3–5* in that they are conducted over 2 weeks and include identical outcome assessments. Assessments performed upon the subjects during post-intervention testing can be found in Figure 2.

#### Study withdrawal

Primary exit or stopping criteria for a given participant in the study includes completion of the study; withdrawal of informed consent (for any reason); an adverse event that, in the opinion of the physician of record, necessitates the participant stopping the study; the loss of ability to freely provide consent through imprisonment or involuntary incarceration for treatment of psychiatric or physical illness; significant non-compliance with the study protocols; or other significant (determined by the PI and physician of record) changes in medications, physical, or mental health.

#### Adverse events

Participants are instructed to inform members of the study team or CTRC staff of any side effects or adverse events. Anticipated mild and moderate adverse events are reported to the IRB on an annual basis. Serious adverse events will be reported to the CU Boulder IRB within 24 h of occurrence. An unanticipated adverse event which meets the CU Boulder IRB definition of an unanticipated problem (i.e., any unanticipated and undesirable effect arising from participation in research that results in an increased risk of harm or injury to a subject, or which suggests the possibility of increased risks to other subjects) will be reported to the CU Boulder IRB using the corresponding form within 5 days of occurrence.

### Statistical analyses

Sample size calculations and pre-determined statistical power for this randomized, double-blind, placebo-controlled, parallel group design clinical trial are based on the primary outcome (FMD_BA_) and the use of the two-sample *t*-test to compare the change in FMD_BA_ between groups following treatment. Preliminary data from our pilot study, which employed a randomized crossover design and was conducted in adults 60–80 years of age, was used to estimate the effect size to calculate sample size for a pre-specified statistical power (Rossman et al., 2018).

Based on the preliminary data from our crossover pilot trial, the increase in FMD_BA_ after treatment with MitoQ was 1.10%; a decrease of −0.38% was observed with placebo control yielding a difference between groups of 1.48% (Rossman et al., 2018). Of note, based on the relation between CVD risk and FMD in the peer-reviewed literature, a clinically meaningful difference in FMD_BA_ is 1.0% (Inaba et al., 2010). As such, the study is powered to achieve a difference in FMD_BA_ 50% greater than that considered to be a clinically meaningful change. The standard deviation of change was estimated as 2.50 and 2.10, respectively, under the two conditions, yielding a pooled standard deviation of 2.31. An effect size of 0.64 was calculated from the mean difference between groups and the pooled standard deviation (1.48/2.31 = 0.64), which was used to determine the required sample size.

At a statistical power of 85%, a two-sample *t*-test to compare the change in FMD_BA_ between groups, and a two-sided significance level of *α* = 0.05, 45 subjects per group (total of 90) is required. To account for a potential dropout of 20% (i.e., the rate observed in our pilot study) a total of 112 [112 (1.0–0.2) = 90] healthy men and women over 60 years of age will be enrolled and equally randomized to the two intervention groups with 56 subjects/group. While our sample size is based on an observed difference in FMD_BA_ that is greater than that considered clinically significant, our sample size has the added benefit of ensuring we are adequately powered to detect a clinically meaningful improvement in the primary outcome should the true effect size be lower than that observed in our pilot study.

Descriptive statistics will be provided for all baseline and outcome variables. The mean and standard error of the mean will be calculated for continuous variables, and proportion will be calculated for categorical or ordinal variables. Median and interquartile range (IQR) will be calculated if a continuous variable is skewed in distribution. The 95% confidence interval will be provided as appropriate. The effect of MitoQ treatment on a given outcome measure will be assessed by a linear regression model, such that post-intervention outcome measures will be regressed against both pre-intervention outcome measures and group randomization. Adjustment for covariates will also be explored.

Every effort will be made to include only participants that complete the trial in the final analysis. Since at least 45 subjects per group are expected to complete the study, a power of 85% or higher is anticipated if the real effect on the primary outcome (FMD_BA_) is similar to that of the pilot study (Rossman et al., 2018), i.e., 0.64. In an unlikely situation in which more than 20% of the enrolled participants drop out of the study, statistical analyses based on the intention-to-treat principle with multiple imputation will be performed. All conclusions will be made using a two-sided significance level of *α* = 0.05. Data transformation will be performed, if appropriate, before further analysis.

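### The protocol says its sample size ensures adequate power for the clinically meaningful FMD difference of 1.0%, but its own sizing inputs give about 53% power there

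*Protocol article*

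**What the plan says.** All the relevant text is in the Statistical analyses section of the protocol article.

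- **Threshold.** Citing the literature on FMD and cardiovascular risk, it states that "a clinically meaningful difference in FMD_BA_ is 1.0" (in percent FMD).
- **Design difference.** The pilot changes of 1.10% on MitoQ and −0.38% on placebo are given as "yielding a difference between groups of 1.48" percent.
- **Variability.** "The standard deviation of change was estimated as 2.50 and 2.10, respectively, under the two conditions", "yielding a pooled standard deviation of 2.31".
- **Sample size.** The effect size is the ratio "1.48/2.31 = 0.64), which was used to determine the required sample size". With a two-sample t-test on the change in FMD, 85% power and "a two-sided significance level of *α* = 0.05, 45 subjects per group (total of 90) is required". To allow for 20% dropout, 112 are to be randomized, 56 per group.
- **Position relative to the threshold.** The section says openly that "the study is powered to achieve a difference in FMD_BA_ 50% greater than that considered to be a clinically meaningful change".
- **The claim at issue.** It closes the sample-size argument by saying that "our sample size has the added benefit of ensuring we are adequately powered to detect a clinically meaningful improvement in the primary outcome", in the event that the true effect is below the pilot's.

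No power figure is given for 1.0% or for any other difference below 1.48%. Further on, the same section anticipates 85% power or more on condition that the real effect is similar to the pilot effect size of 0.64. It also specifies the efficacy model as a regression of the post-intervention value on the pre-intervention value and randomized group.

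**The concern.** The reasoning runs in the wrong direction. For a fixed SD, α and power, a larger design difference needs fewer participants, and those fewer participants give less power for a smaller difference. Sizing on 1.48% when 1.0% is the meaningful threshold therefore costs power at 1.0%. It cannot be an added benefit there.

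What is at stake is how the primary result is read. The trial is meant to establish efficacy and may be the basis for a phase III trial. A reader who accepts the sentence could take a non-significant result as good evidence against a 1.0% effect. On the protocol's own sizing calculation, an effect of exactly that size would be missed about 47% of the time.

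**Working it through.** **Inputs**, all from Statistical analyses: SD of change 2.50 and 2.10; design difference 1.48; meaningful difference 1.0; two-sided α 0.05; two-sample t-test; 45 completers and 56 randomized per group.

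**1. Reproduce the plan's figure.**
- Pooled SD = √((2.50² + 2.10²)/2) = 2.309, stated as 2.31.
- Effect size = 1.48/2.31 = 0.641, stated as 0.64.
- For 85% power, the noncentral t calculation gives n = 44.8 per group at 0.64 (44.7 at 0.641), so 45. Power at 45 per group is 85.2%.

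The stated sample size is therefore correct for 1.48%, and it is the smallest whole number that reaches 85%.

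**2. Same calculation at the meaningful difference.**
- Effect size = 1.0/2.31 = 0.433.
- Standard error with 45 per group = 2.31 × √(2/45) = 0.487, so the noncentrality is 1.0/0.487 = 2.05 (against 1.48/0.487 = 3.04 at the design difference), with a critical t of 1.987 on 88 degrees of freedom.

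| Setting for a true difference of 1.0% | Power |
|---|---|
| 45 per group, SD 2.31 | 52.8% |
| 56 per group (no dropout), SD 2.31 | 62.2% |
| 45 per group, SD 2.10 in both arms | 60.8% |
| 45 per group, SD 2.50 in both arms | 46.7% |

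**3. What 45 per group can detect, and what 1.0% would need (SD 2.31).**
- Smallest true difference with 85% power: 1.48%. With 80% power: 1.38%.
- Power at 1.1%, 1.2% and 1.3%: 61%, 68% and 75%.
- Per-group n for a true 1.0%: about 85 for 80% power and about 97 for 85%.

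**4. Effect of the planned baseline adjustment.** The documents give neither the pre–post correlation r nor the separate pre and post variances. *Assuming* equal variances, the residual SD is 2.31 × √((1 + r)/2).

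| r (assumed) | Residual SD | Power for 1.0%, 45 per group | Power for 1.0%, 56 per group |
|---|---|---|---|
| 0 | 1.63 | 82% | 89% |
| 0.3 | 1.86 | 71% | 80% |
| 0.5 | 2.00 | 65% | 75% |
| 0.7 | 2.13 | 60% | 69% |

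Unequal variances move these figures either way. With 45 per group and r = 0.3, 0.5 and 0.7, power is 82%, 77% and 73% if the post SD is 0.8 times the pre SD, and 64%, 59% and 54% if it is 1.2 times.

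**5. Precision.** The expected 95% CI half-width for the t-test on change is 1.987 × 0.487 = 0.97%. A non-significant estimate above about 1.0 − 0.97 = 0.03% therefore leaves 1.0% inside the interval. By simulation with SD 2.31 and 45 per group, the share of non-significant results that cannot exclude 1.0% is about 47% if the true effect is 0, 79% if it is 0.5%, and 95% if it is 1.0%.

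**The case against.** Four points can be made for the protocol.

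- **The efficacy model is not the t-test.** This has real force. Baseline adjustment should improve on 53%, and step 4 shows combinations that reach 80%: near-zero correlation with 45 per group, r = 0.3 with no dropout, or a post SD clearly smaller than the pre SD. A reader might infer that the trial has only an even chance of detecting 1.0% under its planned analysis, or that adjustment cannot bring power to 80%. The documents support neither inference, because they do not supply the inputs. For the same reason, 60–71% is an illustration under stated assumptions and not a bound. But those missing inputs also mean that nothing in the protocol supports the word ensuring, and the only power calculation it reports is the t-test.
- **A true effect below the pilot's may mean only slightly below.** Power of 80% is kept down to 1.38%. But the sentence speaks of a clinically meaningful improvement, and the same section sets that at 1.0%.
- **An observed 1.0% would just reach significance**, since the critical difference is 0.97%. That is so, but the sentence concerns power at a true effect size.
- **The section is candid elsewhere.** It says the trial is powered for more than the meaningful difference, and it makes the 85% conditional on an effect near 0.64. This limits the harm, but it also contradicts the sentence.

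A reader might also infer that most null results from this trial could not exclude 1.0%. That depends on the true effect: under no effect, slightly more than half of non-significant results would exclude it.

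**Conclusion.** The statement is wrong as written. On the protocol's own sizing inputs (two-sample t-test, SD 2.31, two-sided 0.05), power for the 1.0% difference is about 53% with 45 per group and 62% with 56, against the 85% planned at 1.48%. These figures take the pilot SD at face value, as the protocol does; neither of the two pilot SDs used alone brings power at 1.0% to 80% with 45 per group. The planned regression would add power by an amount that the documents do not allow one to fix, so the supportable conclusion is that adequate power at 1.0% is not ensured, not that it is impossible. The sample-size calculation for 1.48% is sound, and the sample size, test and α do not rest on the faulty sentence. The error matters because it states a property of the primary analysis that the design has not been shown to have, and because it bears on how a null result is read.

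**What to change.** Delete the sentence and put in its place: *With 45 per group the trial has 85% power for a difference of 1.48%, 80% power for 1.38% and about 53% power for 1.0% (two-sample t-test); baseline adjustment may increase this.*

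Optionally, add that a non-significant primary result will be read from its 95% CI (expected half-width about 0.97% for the t-test on change) against 1.0%, and not as showing that a clinically meaningful effect is absent. If a figure for the adjusted analysis is wanted, the pre–post correlation and the two variances it assumes should be given with it.

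The cost is a few lines of text and a less favourable description of the design. No change to the sample size, the analysis or the conduct of the trial is asked for.

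### The stated treatment-effect model leaves out sex and age group, on which randomisation was blocked; if these predict FMD given baseline, the test is slightly conservative and loses a little power

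*Protocol article*

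**What the plan says.** Under Randomization and blinding, the protocol article reports of the pilot study that "we did not observe an obvious effect of subject (biological) sex or age on the change in FMD_BA_ with active treatment". It then says that the pilot, with 20 participants, was probably too small to show such effects, and that "NIH requires that sex and other biological factors that may influence responsiveness be included in the analysis plan". The next sentence presents the design as the consequence: "block randomization has been employed based on biological sex (men and women) and age (60–70 years and >70 years".

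Under Statistical analyses, the effect of treatment on each outcome is to come from a linear regression in which "post-intervention outcome measures will be regressed against both pre-intervention outcome measures and group randomization". The sentence that follows reads "Adjustment for covariates will also be explored"; it names no covariate. On the test level, "All conclusions will be made using a two-sided significance level of *α* = 0.05". The sample size in the same section rests on a two-sample t-test of the change in FMD, which has no strata either.

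**The concern.** The two sections do not fit together. One says that factors such as sex belong in the analysis plan and answers that with a blocked randomisation; the other prints a model without those factors and makes no commitment to add them.

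There is also a statistical consequence. Blocking within four sex-by-age strata keeps the arms alike on those factors, so differences between strata contribute little to the true sampling variation of the treatment difference. A model without the strata still counts those differences as residual noise. If the strata predict the outcome after baseline adjustment, the reported standard error is larger than the true one, the confidence interval is too wide, and precision already secured by the design is not used. If they do not predict it, nothing is lost.

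**Working it through.** **Inputs from the protocol article (Statistical analyses; Randomization and blinding).** Mean difference 1.48; SDs of change 2.50 and 2.10; effect size 0.64; two-sided α 0.05; 45 per group analysed; 112 enrolled with 20% dropout; strata sex × age (60–70, >70).

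**Assumed.** R² is the share of the variance of post-treatment FMD, left after baseline FMD and group, that sex and age stratum explain. The article gives no value; 0 to 0.10 is used here.

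**1. The plan's own figure.** Pooled SD = √((2.50² + 2.10²)/2) = 2.31, and 1.48/2.31 = 0.64. A two-sample t-test (noncentral t) at 0.64 needs 45 per group and gives 85.1% power. The stated figure reproduces. The normal approximation at 45 per group gives 85.9%; it is the reference for step 2.

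**2. Effect of leaving the strata out, with perfect balance within strata.**

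- Model SE / true SE = 1/√(1 − R²)
- Actual type I error = 2 × P(Z > 1.96/√(1 − R²))
- With δ = 0.64 × √(45/2) = 3.036, power without strata = Φ((δ − 1.96)/√(1 − R²))
- Power with strata = Φ(δ/√(1 − R²) − 1.96)

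The value 0.64 is kept throughout, as if adjusting for baseline gained nothing over analysing the change.

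| R² | Model SE / true SE | Type I error | Power without strata | Power with strata | Points lost |
|---|---|---|---|---|---|
| 0 | 1.000 | 5.0% | 85.9% | 85.9% | 0 |
| 0.03 | 1.015 | 4.7% | 86.3% | 86.9% | 0.6 |
| 0.05 | 1.026 | 4.4% | 86.5% | 87.6% | 1.1 |
| 0.10 | 1.054 | 3.9% | 87.2% | 89.3% | 2.1 |

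**3. Simulation without dropout.** 90 patients, blocks of 4 within strata, half men, 40% over 70 (all assumed), 8,000 runs per setting:

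- R² = 0: type I error 4.9%; power 83.6% with or without the strata.
- R² = 0.05: SE ratio about 1.03; type I error 4.3%; power 85.3% without and 86.7% with the strata.
- R² = 0.10: SE ratio 1.05 to 1.07; type I error 4.1%; power 86.4% without and 88.6% with the strata.

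Direction and size agree with step 2.

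**4. Allowance for dropout.** Take a stratum of m randomised patients, balanced by blocks, with 20% lost at random. The variance of the arm-size difference among those left is m × 0.2 × 0.8 = 0.16m. Under simple randomisation it would be 0.8m for the same 0.8m patients. So 0.16/0.8 = 0.2 of the imbalance returns, and the SE ratio becomes 1/√(1 − 0.8R²): 1.012 at R² = 0.03 and 1.043 at R² = 0.10. A simulation of 112 randomised and 90 analysed (equal strata, blocks of 4, random dropout, all assumed) gave about 1.01 and 1.04, with type I error of about 4.9% and 4.1%. The SE ratios in step 2 are therefore upper bounds for their R².

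**The case against.** The strongest objection is that no loss has been shown. A reader might infer that the standard error is overstated as a matter of fact. The article does not support that: it gives no figure for how sex or age predicts post-treatment FMD given baseline, the baseline term may already absorb part of any such effect, and at R² = 0 the standard error is right. This stands, and the size is therefore given as a range that includes zero. The pilot remark does not settle the matter the other way. It concerns the change in FMD with active treatment, in a sample that the authors themselves call too small. Moreover, if strata differ by Δ in FMD level both before and after treatment, a baseline slope b below 1 leaves (1 − b)Δ unexplained even though the change is unrelated to stratum.

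The effect is also small and in the safe direction. This stands too: in the table, power without the strata never falls below the planned 85%.

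Three stronger readings are tempting and go too far:

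- *The stated requirement is never met, or sex and age have no planned analysis.* The requirement is placed on the analysis plan, which is not shown. A journal article commonly leaves covariate lists and subgroup analyses to that plan.
- *Sex and age must be main effects in the primary model.* The cited requirement speaks of factors that may influence responsiveness, which is closer to effect modification. The case for main effects rests on the blocked randomisation.
- *The adjusted result will be picked after the data are seen.* A definite model is stated; the exploration is additional, and nothing says that it would replace that model.

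The objections leave one thing untouched: the article prints a specific model, and that model omits the factors used to randomise.

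**Conclusion.** The point holds as an inconsistency between two sections, with a modest and conditional statistical cost. For an assumed partial R² of 0 to 0.10, the model standard error is too large by 0 to at most about 5% (about 4% at the top of the range once 20% random dropout is allowed for), the actual type I error lies between 5% and about 3.9%, and 0 to about 2 percentage points of power are lost. The treatment estimate is unbiased and false positives do not become more likely. The 45 per group stands, because it was derived from an unadjusted t-test. The result rests on the assumed R² range and on strata that stay close to balanced among those analysed. The validity of the trial is not threatened; the change is worth making because it costs almost nothing and brings the model into line with the randomisation.

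**What to change.** In Statistical analyses, state the primary model as 3-month FMD regressed on group, baseline FMD, sex and age stratum (60–70, >70), and label any other covariate set as sensitivity. With 90 analysed, residual degrees of freedom go from 87 (intercept, group, baseline) to 85. No new data are needed and the sample size is unaffected.

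Group-by-sex and group-by-age-stratum estimates with 95% confidence intervals are optional. The trial is sized for the main effect only, so they would be descriptive, and they may already be in the analysis plan that is not shown. If that plan already has sex and age stratum in the primary model, it is enough to bring the article's model sentence into line with it.

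### Completers are the default analysis population, and intention-to-treat applies only above a dropout level that the plan itself expects to reach

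*Protocol article*

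**What the plan says.** Two adjacent statements in the protocol article, Statistical analyses, together set the analysis population. The default is "Every effort will be made to include only participants that complete the trial in the final analysis". The exception is "In an unlikely situation in which more than 20% of the enrolled participants drop out of the study, statistical analyses based on the intention-to-treat principle" and multiple imputation will be used. No other section names an intention-to-treat primary analysis.

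The sample size text in the same section plans for the same dropout figure: "To account for a potential dropout of 20% (i.e., the rate observed in our pilot study) a total of 112" participants, who "will be enrolled and equally randomized to the two intervention groups with 56 subjects/group".

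Randomization and blinding places randomisation after screening and baseline testing. Study withdrawal lists reasons for leaving that include adverse events, "significant non-compliance with the study protocols", and significant changes in medication or health. Potential side effects names gastrointestinal distress as the expected effect of MitoQ. FMD is also measured at 6 weeks (Visit 7).

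**The concern.** Baseline testing is finished before allocation, so every later loss is a post-randomisation loss. Several listed exit reasons can be influenced by the assigned treatment. If the two arms lose different kinds of participants, the completers compared are no longer the groups that randomisation made comparable, and the regression on baseline FMD and group corrects only for what baseline FMD explains. The plan accepts this for any dropout up to 20%.

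Above 20%, both population and method change. The question being answered (the effect in those who finish, or the effect of assignment) therefore stays open until dropout has been counted. The plan treats that change as remote, although its own dropout assumption sits exactly at the trigger. At stake is the primary efficacy conclusion of a trial intended to establish efficacy and to support a phase III study.

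**Working it through.** **1. The plan's own figures (Statistical analyses).** Difference 1.48; SDs of change 2.50 and 2.10; power 85%; two-sided alpha 0.05; 45 completers per group; 112 enrolled.

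- Pooled SD = √((2.50² + 2.10²)/2) = 2.31. Effect size = 1.48/2.31 = 0.64.
- Exact two-sample t-test power at 0.64 is 84.3% with 44 per group and 85.1% with 45. The stated 45 reproduces.
- 90/(1 − 0.20) = 112.5, against 112 stated (112 × 0.8 = 89.6). The difference is immaterial.

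The sample size arithmetic is not at fault.

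**2. Uncorrected exclusions.** 20% of 112 is 22.4, so intention-to-treat starts at 23 dropouts. Up to 22 of 112 (19.6%) can be excluded under the default rule.

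**3. Chance of passing the trigger.** P(X ≥ 23), with X ~ Binomial(112, p). The plan's own rate is p = 20%; the other rates are assumptions that show the range.

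| True dropout rate | P(at least 23 of 112) |
|---|---|
| 15% | 7% |
| 18% | 28% |
| 20% | 48% |
| 22% | 68% |
| 25% | 89% |

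**4. What informative dropout could do (assumed; not in the documents).** No true effect, SD 2.31, 56 per arm, 20% dropout per arm. A latent tendency to drop out has correlation ρ with poor FMD response in the MitoQ arm; placebo dropout is random.

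- Keeping the upper 80% of a standard normal shifts its mean by φ(0.842)/0.80 = 0.280/0.80 = 0.35.
- Bias = ρ × 0.35 × 2.31, which is 0.24 FMD percentage points at ρ = 0.3 and 0.40 at ρ = 0.5. Simulation gives 0.24 and 0.40 to 0.41.
- Simulated type I error is about 8% at ρ = 0.3 and 13% to 14% at ρ = 0.5.
- With the same mechanism in both arms, bias is about 0 and type I error about 5%.

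**5. How much of this an all-randomised analysis removes.** In the ρ = 0.5 case, imputing within arm from baseline leaves the bias at about 0.41. If every dropout had a 6-week value correlating 0.5 with the final response (assumed), about 0.31 would remain.

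**6. Power with all 112 analysed.** These figures assume that outcomes are obtained for everyone; imputed data would give somewhat less. With 20% non-completers who keep a fraction f of the effect, the difference is 1.48 × (0.8 + 0.2f).

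| f | Difference | Effect size | Power, 56 per group |
|---|---|---|---|
| 1 | 1.48 | 0.64 | 91.9% |
| 0.5 | 1.33 | 0.576 | 85.6% |
| 0 | 1.18 | 0.512 | 76.6% |

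**The case against.** The kindest reading is that the completers sentence is a clumsy promise to maximise retention. That does not stand, because a conditional intention-to-treat clause would be unnecessary if intention-to-treat were the default. Nor is this a detail left to an analysis plan: the article states the rule.

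Several stronger readings are tempting, and on these the other side is right.

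- *The sponsor could choose between two results.* The rule fixes one analysis on each side of the threshold. The trigger is overall dropout, and those acquiring and analysing outcomes are blinded. It is a poor rule, but it gives no licence to pick by outcome.
- *Randomisation is broken.* The allocation procedure is sound, analysed participants stay in their assigned arm, and nothing excludes completers for imperfect pill counts. The defect is the uncorrected omission of randomised people.
- *Completer analysis favours MitoQ.* The positive bias above comes from letting poor responders leave one arm only. The tolerability evidence is mild: minor gastrointestinal distress at 20 mg in the pilot, and no dropout from side effects at the acute 160 mg dose. Bias remains possible; its direction is not shown.
- *A 6-week pilot understates dropout over 3 months.* The pilot was a crossover, and the article does not say over what total period its 20% arose.
- *Changing the population cures the problem.* It does so only in part (step 5). Also, the gap between 1.48 and 1.18 in step 6 is partly a difference in the question asked, and imputation that treats dropouts like completers would not recover 1.18.

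**Conclusion.** The point holds as a defect in a stated rule. Completers are the default population, up to 22 of 112 randomised participants can be dropped without correction, and population and method turn on the observed overall dropout count. Calling the trigger unlikely conflicts with the plan's own 20% assumption: at that rate the switch is close to a coin toss (48%), and it ranges from 7% to 89% for true rates of 15% to 25%. These probabilities assume independent dropout and 112 randomised.

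The documents do not fix the direction or size of any bias. The figures of about 0.24 to 0.41 FMD percentage points and 8% to 14% type I error illustrate one assumed, one-sided mechanism. Against the 1.0% that the plan treats as clinically meaningful, bias of that size would matter.

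**What to change.** - Define the primary analysis as all randomised participants in their assigned arm, whatever the dropout rate.
- Prespecify the handling of missing FMD: a repeated-measures model of 6-week and 3-month FMD with baseline FMD as covariate, or multiple imputation that uses baseline and 6-week FMD.
- Keep the completer analysis as a sensitivity analysis. Delete the 20% trigger and the word *unlikely*.
- State that the primary analysis assumes data missing at random and only partly removes bias from informative dropout. Add a sensitivity analysis for departures from that assumption, for example delta-adjusted imputation.
- Optionally, through an IRB amendment, invite participants who stop treatment and still consent to attend the outcome visits already scheduled. The stopping criteria stay as they are. This is the only step that supplies the missing outcomes themselves.

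Cost: revised wording, a little more analysis work, and possibly a slightly less favourable estimate. The 6-week FMD is already part of the schedule. The optional follow-up needs IRB approval and carries some visit cost; the article gives no budget from which to judge it. Planned enrolment need not change if non-completers keep at least about half the effect and most outcomes are obtained.
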